### 6.3 FIDELITY

**Interventionist Training and Tracking:** To ensure intervention fidelity, regular training, supervision, and monitoring will be implemented. The intervention will be delivered using the existing infrastructure and resources of the Health and Wellness Centres (HWCs). Study team facilitators will ensure adherence to protocols through:

- **Training:** Consistent and thorough training for all interventionists to maintain standard delivery practices.
- **Supervision:** Ongoing supervision by the study team to oversee intervention implementation.
- **Monitoring:** Routine monitoring to track adherence to the planned intervention protocol.

**Daily Intervention and Health Diary:**

- Each patient will receive a daily administered intervention and a health diary for recording their daily intake or practice of the intervention.
- The health diary will include detail doses, frequency, timing, and other relevant information.
- Participants are required to update the health diary daily.
- Investigators will collect and review health diary data monthly during contact sessions.

**Follow-up Assessments:**

- Comprehensive follow-up assessments will occur every six months at the health facility, where participants will undergo outcome evaluations.

## 6.4 MEASURES TO MINIMIZE BIAS

### Randomization and Blinding

- **Randomization:** PHCs will be randomized to intervention or control groups to reduce selection bias.

- **Observer Blinding:** Outcomes will be assessed by blinded evaluators to minimize measurement bias.

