**CTRI Registration: CTRI/2024/09/073487**

## 1.2 SCHEMA

- i. **Enrollment:**
  - a. Screening for eligibility using the MAQ-PC plus tool, frailty index and DART test.
- ii. **Randomization:**
  - a. Clusters (PHCs in Bhubaneswar) randomly assigned to either:
    - i. **Intervention Group:** Multi-FrAME package
    - ii. **Control Group:** Standard routine care
- iii. **Intervention Components (Multi-FrAME):**
  - a. Medical management
  - b. Nutritional support
  - c. Physiotherapy and physical activity
  - d. Psychosocial counseling
- iv. **Data Collection Time Points:**
  - a. Baseline
  - b. Follow-up at 6 months
  - c. Follow-up at 12 months
- v. **Outcome Measures:**
  - a. **Primary:** EQ-5D-5L index scores
  - b. **Secondary:** Frailty index, ADL/IADL scores, healthcare utilization/expenditure, patient satisfaction, medication adherence, mortality
- vi. **Monitoring and Safety:**
  - a. Monthly contact sessions for intervention fidelity and data collection
  - b. Continuous monitoring of AEs and SAEs
  - c. Training of all sites on identifying AE/SAE
  - d. Overview by DSMB
- vii. **Analysis:**
  - a. Intention-to-treat approach

- b. Interim analysis after 50% completion of the 12-month follow-up
- viii. **Completion:**
  - a. Endline assessments at 12 months
  - b. Data analysis and dissemination of findings

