## 4 STUDY DESIGN

### 4.1 OVERALL DESIGN

This is a phase 3 cluster randomized, parallel arm, observer-blinded trial. The clusters will be urban Primary Healthcare Centres (PHCs- but also known as Health and Wellness Centres or Ayushman

Arogya Mandirs) in Bhubaneswar city, randomly assigned to either the Multi-FrAME intervention or standard care.

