## 4.2 SCIENTIFIC RATIONALE FOR STUDY DESIGN

The use of a cluster randomized design is essential in this trial to effectively evaluate the Multi-FrAME intervention's impact within the urban Primary Healthcare Centres (PHCs) of Bhubaneswar city. Given the nature of the intervention, which includes various components at the healthcare center level, randomizing at the cluster level reduces contamination risks between participants receiving the intervention and those receiving standard care.

This design is particularly relevant in the context of Bhubaneswar's urban PHCs, where healthcare practices can vary significantly. By employing a cluster approach, the trial can assess the intervention in a way that mirrors real-world application, enhancing external validity. Randomization at the PHC level allows for the capture of data reflecting the complex interactions and systemic changes induced by the intervention. This will also improve future possibility of uptake into systems as the intervention is being tested at the point of proposed delivery through the system.

The observer-blinded aspect of the study further strengthens its validity by reducing assessment bias. Blinding ensures that outcome evaluators remain unaware of which group (intervention or control) the participants belong to, thus minimizing potential biases in data collection and interpretation.

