## 12.2 SAMPLE SIZE DETERMINATION

- **Assumptions:**

- Mean Quality of life utility scores of control group = 0.87 [SD=0.17] (Jyani et al., 2023)
- Effect size: Based on anticipated (clinically meaningful) improvement of 10% in HRQoL scores ([name] et al., 2025)
- Power: 90%
- Significance level: 0.05
- Intra-cluster correlation: 0.24 ([name] et al., 2023)
- Attrition rate: 25%

- **Calculation Methodology:** The following steps were used for the calculation of sample size

1. Effect size calculation

Effect size is the standardized mean difference between the control and intervention groups: calculated using the following formula,

$$Effect\ Size\ (Cohen's\ d) = \frac{Mean\ difference\ (Improvement)}{SD}$$

2. Sample size for two sample t-tests

The formula to calculate the sample size for a two-sample t-test is based on the following

$$n = \frac{(Z_{1-\alpha/2} + Z_{1-\beta})^2}{d^2} * \frac{2(SD)^2}{Effect\ size}$$

Where:

- $Z_{1-\alpha/2}$  is the critical value for a two-tailed test at the significance level  $\alpha$ .
- $Z_{1-\beta}$  is the critical value corresponding to the desired power  $(1-\beta)$ .
- $d$  is the effect size.
- $SD$  is the standard deviation

The `pwr.t.test()` function in R is used to perform this calculation, which outputs the required sample size for each arm of the trial assuming a simple t-test.

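### Allocation is described only as randomisation of PHCs, with no balance constraint, although the plan expects PHCs to differ and assumes an ICC of 0.24

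*Protocol*

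**What the plan says.** Allocation is described in three places in the Protocol. Section 1.2 (Schema) has "Clusters (PHCs in Bhubaneswar) randomly assigned to either" one of the two groups. Section 4.1 has the PHCs "randomly assigned to either the Multi-FrAME intervention or standard care". Section 6.4, which deals with bias control, has "PHCs will be randomized to intervention or control groups to reduce selection bias". None of them names stratification, matching, minimisation or constrained randomisation, and none says that allocation is unrestricted.

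Section 4.2 supports the cluster design by describing the city's PHCs as a setting "where healthcare practices can vary significantly". Section 12.2 lists "Intra-cluster correlation: 0.24", a control mean of 0.87 with SD 0.17, 90% power, and "Effect size: Based on anticipated (clinically meaningful) improvement of 10% in HRQoL scores". Its formulae use the cluster size and the number of clusters, but neither is given a value.

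Section 12.4.1 plans mixed-effects models to allow for clustering. No baseline or PHC-level covariate is named there or in section 12.4.2. The schedule in section 1.3 puts randomisation and the baseline EQ-5D-5L in the same month-0 column and does not fix their order.

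**The concern.** When a plan expects its clusters to differ and assumes a large ICC, it should say how allocation deals with that. Here it describes nothing beyond random assignment. If few PHCs are allocated, the arms can differ noticeably in their underlying PHC means before any intervention starts. That widens the interval on the primary endpoint and makes the result harder to defend. The allocation method is a design decision that has to be fixed before PHCs are assigned, and it cannot be repaired in a later analysis plan.

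**Working it through.** **Inputs from section 12.2:** control mean 0.87, SD 0.17, ICC 0.24, power 90%, two-sided alpha 0.05, improvement 10%. Reading the 10% as relative, the target is 0.10 × 0.87 = 0.087, and half of it is 0.0435. **Assumptions:** 1:1 allocation, equal PHC sizes, normal PHC effects, and an ICC and SD that apply to the EQ-5D-5L index. The plan states no sample size, so there is no figure of its own to reproduce.

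**Step 1, spread between PHCs.** √0.24 × 0.17 = 0.083, against a target of 0.087.

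**Step 2, chance difference between arms.** With k PHCs per arm, the SD of the difference in true PHC means is 0.0833 × √(2/k). The probability of a difference beyond ±0.0435 is:

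| k per arm | SD of difference | Probability, either direction |
|---|---|---|
| 5 | 0.0527 | 41% |
| 10 | 0.0372 | 24% |
| 15 | 0.0304 | 15% |
| 20 | 0.0263 | 10% |
| 25 | 0.0236 | 6.5% |
| 30 | 0.0215 | 4% |

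The chance of an imbalance favouring the intervention is half of each figure: about 5% at 20 per arm, 12% at 10 and 20% at 5.

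**Step 3, which k fits the plan.** With d = 0.087/0.17 = 0.512, a t-test needs 81.2 per arm without clustering. The PHCs needed per arm are 81.2 × [1 + (m − 1) × 0.24]/m, where m is the number analysed per PHC. This gives 22.6 at m = 20 and 20.7 at m = 50. As m grows it falls towards 81.2 × 0.24 = 19.5. So 90% power needs at least 20 PHCs per arm whatever their size, and the lower rows of the table are the ones consistent with the plan's assumptions.

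**Step 4, what balancing does to the imbalance.** No document figure gives the share of between-PHC variance that the balancing factors would explain. If it were 50%, the probability would fall from 41% to 24% at 5 per arm, from 24% to 10% at 10, and from 10% to 2% at 20. If it were 25%, the results would be 34%, 18% and 6%.

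**Step 5, what balancing does to precision.** This was simulated with 20 PHCs per arm, 15 participants per PHC, and baseline to 12-month correlations of 0.8 at PHC level and 0.5 within person. Constrained allocation means drawing from the best-balanced tenth of candidate allocations on baseline PHC mean. The cluster numbers and correlations are assumptions. SD of the estimated 12-month difference:

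| Allocation and analysis | SD | Variance reduction against first row |
|---|---|---|
| Unrestricted, unadjusted | 0.0292 | – |
| Unrestricted, change score | 0.0210 | 1 − (0.0210/0.0292)² = 48% |
| Unrestricted, baseline-adjusted | 0.0200 | 1 − (0.0200/0.0292)² = 53% |
| Constrained | 0.0192 | 1 − (0.0192/0.0292)² = 57% |

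Beyond baseline adjustment, constrained allocation removes a further 1 − (0.0192/0.0200)² = 8% of variance. A separate run of 4,000 replicates gave 0.0194 against 0.0191, or 3%. Simulated SDs carry random error, so a few percent to about 12% is a fair range.

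**The case against.** The strongest reply is that the protocol is silent rather than wrong. It never says that allocation is unrestricted, and the manual of operating procedures listed in section 17 is not shown. That stands against saying that the plan has chosen simple randomisation. It does not answer the point that section 6.4 describes no restriction where one would be expected.

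Second, chance differences between PHCs are what the design effect in section 12.2 and the mixed models in section 12.4.1 allow for. This also stands. A reader might infer that an imbalance would bias the result or raise type I error. With a cluster-adjusted analysis it does neither. The proviso matters, because section 12.4.2 also lists t-tests for the primary comparison, and an ordinary individual-level t-test would not carry the between-PHC variation in its standard error.

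Third, a reader might take the 24% at 10 PHCs per arm as the risk in this trial. The documents do not give the number of PHCs, and 10 per arm could not deliver the plan's stated power.

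Fourth, a reader might credit constrained allocation with the whole 57% fall in variance. That figure applies only to an unadjusted comparison. The endpoint in section 3 is change in EQ-5D-5L, and adjusting for baseline captures most of the gain without any change to allocation.

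Finally, section 4.2 speaks of healthcare practice, not EQ-5D-5L, and the ICC is a planning assumption. The calculation shows what the plan's own assumptions imply. It does not establish how much these PHCs differ in quality of life.

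**Conclusion.** The point holds in a limited form. The protocol expects PHCs to differ, assumes an ICC that puts the between-PHC SD close to the target effect, and describes no balance at allocation. Its importance depends on a number that the protocol omits. With 20 or more PHCs per arm, the chance of an imbalance larger than half the target is about 10% or less in either direction. With 10 to 5 per arm it is 24% to 41%, and such a design would also miss its stated power.

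The loss is in precision and credibility, provided that the primary analysis adjusts for clustering. Restricted allocation is the better method, with a modest gain once baseline is in the model. The conclusion rests on the relative reading of the 10%, equal PHC sizes, 1:1 allocation and the assumed ICC. The precision figures rest also on the assumed correlations.

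**What to change.** - **Section 6.4:** state the number of PHCs per arm and allocate them by stratified or covariate-constrained randomisation on two or three PHC factors known beforehand, such as catchment or attendance size and staffing. Use the baseline PHC mean EQ-5D-5L only if baseline is finished before allocation, and in that case fix the order in section 1.3. With constrained randomisation, draw one allocation at random from the acceptably balanced set.
- **Section 12.4.2:** include those factors and baseline EQ-5D-5L in the primary mixed model. Leaving the balancing factors out would make the test conservative.

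The cost is a short allocation program, a few sentences of text, and some PHC-level data collected before allocation. A few degrees of freedom are also used. With 20 PHCs per arm, three PHC-level factors reduce 40 − 2 = 38 to 35, which matters little. With 5 per arm they reduce 10 − 2 = 8 to 5, so with that few PHCs fewer factors should be chosen.

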#### 6.5 STUDY INTERVENTION/EXPERIMENTAL MANIPULATION ADHERENCE

- **Data Collection:** Monthly collections from the Health Diary during contact sessions to ensure adherence and fidelity.
- **Monthly Check-ins:** Provide additional support and address any barriers to compliance.

### 7 CONCOMITANT THERAPY

Participants are advised to continue any existing prescribed therapies unless contraindicated by the trial protocol.

### 8 DISCONTINUATION AND PARTICIPANT DISCONTINUATION/WITHDRAWAL

#### 8.1 DISCONTINUATION OF STUDY INTERVENTION/EXPERIMENTAL MANIPULATION:

Participants may discontinue the intervention under the following circumstances:

- **Adverse Events:** If a participant experiences an adverse event that poses a risk to their health or well-being, determined by the investigator, intervention may be paused or discontinued.
- **Non-compliance:** Repeated non-compliance with the intervention protocol may lead to discontinuation after consultative discussions by the study team.
- **Participant Request:** Participants can voluntarily withdraw from the intervention at any time without affecting their standard medical care.
- **Investigator's Decision:** The investigator may decide to discontinue the intervention if it's in the participant's best interest, based on emerging safety data or other concerns.

#### 8.2 PARTICIPANT DISCONTINUATION/WITHDRAWAL FROM THE STUDY:

Participants may withdraw from the study due to:

- **Voluntary Withdrawal:** Participants have the right to withdraw consent and discontinue participation at any stage. They will be encouraged to complete a final assessment for safety data.
- **Loss to Follow-up:** If participants miss three consecutive scheduled visits and cannot be contacted despite reasonable efforts, they will be considered lost to follow-up.
- **Discovery of Ineligibility:** If found ineligible during the study, participants will be withdrawn, and the reasons documented.

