### 8.3 PROCEDURES FOR DISCONTINUATION/WITHDRAWAL

- **Documentation:** All discontinuations or withdrawals will be documented, including the reason and date.
- **Data Management:** Data collected up to the point of withdrawal will be retained and used in analyses unless the participant requests otherwise.
- **Continuous Communication:** Study staff will maintain regular communication to address concerns and potentially prevent withdrawal.

The principles of respect, safety, and voluntary participation will guide all decisions related to discontinuation and withdrawal. Participants will receive appropriate counselling and support throughout this process.

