### 12.3 POPULATIONS FOR ANALYSES

The analysis will use the Intention-to-Treat (ITT) approach, which includes all randomized participants, regardless of their level of adherence to the intervention or any withdrawals from the study. This method preserves the benefits of randomization, allowing an assessment of the intervention's effectiveness under real-world conditions by accounting for typical variations in participant behaviour and engagement. By including all randomized individuals, the ITT analysis offers a realistic estimate of the intervention's impact on the general population represented in the study.

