#### 12.4.8 SUB-GROUP ANALYSES

- **Objective:** To explore differential effects of the Multi-FrAME intervention among various participant subgroups, providing deeper insights into specific population benefits.
- **Subgroups of Interest:**
  - **Age Categories:**
    - <70 years
    - ≥70 years
  - **Gender:**
    - Male
    - Female
  - **Baseline Frailty Level:**
    - Mild frailty (Frailty Index < 0.30)
    - Moderate frailty (Frailty Index ≥ 0.30)
  - **Comorbidity Categories:**
    - 2-3 chronic conditions
    - >3 chronic conditions
  - **Adherence to interventions-** each component
  - **Sensitivity analysis by excluding contamination of control arm** - If any interventions are received/taken by themselves in the control arm participants

- **Analysis Methods:**
  - **Statistical Approach:** Use interaction terms in regression models to examine variations in treatment effects across subgroups.
  - **Outcome Measures:** Analyze primary and secondary outcomes within each subgroup, focusing on health-related quality of life, frailty index, and healthcare utilization.
- **Interpretation:**
  - Identify trends that may indicate which subgroups benefit most from the intervention.
  - Consider clinical significance alongside statistical significance to guide potential tailoring of interventions in future applications.
- **Reporting:**
  - Subgroup findings will be reported in terms of effect sizes and confidence intervals to highlight meaningful differences.
  - These analyses will be exploratory and not adjusted for multiple comparisons, interpreted cautiously.

---

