## 15 ABBREVIATIONS AND SPECIAL TERMS

- **PHC:** Primary Healthcare Centre
- **EQ-5D-5L:** EuroQol 5-Dimensions, 5 Levels
- **MAQ-PC:** Multi-Condition Assessment Questionnaire for Primary Care
- **DART:** Dementia Assessment Rapid Test
- **ICMR:** Indian Council of Medical Research
- **RMRC:** Regional Medical Research Centre
- **HWC:** Health and Wellness Centre
- **EDC:** Electronic Data Capture

- **DBMS:** Database Management System
- **PI:** Principal Investigator
- **DMC:** Data Monitoring Committee
- **SOPs:** Standard Operating Procedures
- **ICT:** Information and Communication Technology
- **QA/QC:** Quality Assurance/Quality Control
- **ICC:** Intraclass Correlation Coefficient
- **SAE:** Serious Adverse Event
- **AE:** Adverse Event
- **PROMs:** Patient-Reported Outcome Measures
- **ADL/IADL:** Activities of Daily Living/Instrumental Activities of Daily Living
- Protocol Amendment History- NA

List of CRFS for the trial

| CRF                      | Purpose                                       | Time Point    | Key Constructs/Variables                                                                              |
|--------------------------|-----------------------------------------------|---------------|-------------------------------------------------------------------------------------------------------|
| Eligibility CRF          | Assess participant eligibility                | Screening     | Inclusion/exclusion criteria, consent status                                                          |
| Recruitment/Baseline CRF | Collect initial participant data              | Baseline      | Demographics, baseline health status, medical history                                                 |
| Follow-up CRF            | Track ongoing participant status and outcomes | 6, 12, months | Health-related quality of life, frailty index, ADL/IADL, medication adherence, healthcare utilization |

[figure not shown]

|                                            |                                               |              |                                                                |
|--------------------------------------------|-----------------------------------------------|--------------|----------------------------------------------------------------|
| Exit CRF                     | Record reasons for study exit                 | Upon exit    | Mortality, migration, withdrawal of consent, ineligibility     |

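### Participants found ineligible after enrolment stay in the intention-to-treat set but lose their later outcomes, and adherence is listed for a treatment interaction that cannot be estimated

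*Protocol*

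**What the plan says.** **Ineligibility.** Section 8.2, on leaving the study as distinct from stopping the intervention, says: "If found ineligible during the study, participants will be withdrawn, and the reasons documented". The Exit CRF in the section 15 list gives these exit reasons: "Mortality, migration, withdrawal of consent, ineligibility". Section 8.3 adds: "Data collected up to the point of withdrawal will be retained and used in analyses unless the participant requests otherwise". Section 12.3 adopts an ITT approach, "which includes all randomized participants, regardless of their level of adherence to the intervention or any withdrawals from the study".

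**Adherence.** Section 12.4.8 lists age, gender, baseline frailty and number of chronic conditions as subgroups, and then "Adherence to interventions", for each component. Its method is: "Use interaction terms in regression models to examine variations in treatment effects across subgroups". The same section calls these analyses exploratory. Section 12.4.1 gives adherence as an example of a mediator.

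**Contaminated controls.** The next item in the 12.4.8 list is "Sensitivity analysis by excluding contamination of control arm", with the condition "If any interventions are received/taken by themselves in the control arm participants".

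**The concern.** The ITT promise depends on outcomes as well as on membership of the analysis set. A participant withdrawn for ineligibility at month 7, say, still counts as randomised but has no 12-month EQ-5D-5L value. The loss is imposed by the plan and is avoidable.

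It may also be informative. The exclusion criteria in section 5.2 include dementia, bedridden status and severe mobility impairment, which lie close to what EQ-5D-5L measures. The inclusion criteria in section 5.1 require a frailty index of at least 0.25, and that index is measured again at 6 and 12 months. If the rule covers changes in status after enrolment, withdrawal depends on how the participant is doing.

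The adherence item is a different fault. A subgroup factor for a treatment interaction has to be defined in both arms and fixed before treatment can affect it. Adherence to the package is neither, so the fitted term would not describe how the treatment effect varies.

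**Working it through.** **1. What happens to a participant found ineligible**

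- Section 12.3: in the ITT set, whatever the withdrawal status.
- Section 8.2 and the Exit CRF: out of the study.
- Section 8.3: data before withdrawal are kept and analysed; none are collected afterwards.
- Section 8.2 encourages a final assessment after voluntary withdrawal, but says nothing of the kind for ineligibility.

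Together, the analysis set is intact and the later outcomes are missing.

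**2. Direction**

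- A participant who becomes bedridden and is withdrawn takes a probable poor outcome out of the arm.
- A participant whose frailty index falls below 0.25 and is withdrawn takes a probable good outcome out.

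The wording admits both, so no direction follows.

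**3. Size, illustration only**

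The protocol gives no rate of late ineligibility, so the inputs are assumed. Let p be the share of one arm losing the 12-month value, and g the absolute difference in mean utility between those lost and those remaining. If the remaining mean is R and those lost score lower, the full-arm mean is (1 − p)R + p(R − g) = R − pg. The available-case mean is therefore shifted by p × g, with the sign reversed if those lost score higher.

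The target is the 10% improvement on 0.87 in section 12.2, read as relative: 0.10 × 0.87 = 0.087.

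| p | g | p × g | share of 0.087 |
|---|---|---|---|
| 2% | 0.1 | 0.002 | 2% |
| 5% | 0.2 | 0.010 | 11% |
| 10% | 0.3 | 0.030 | 34% |

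These are shifts in an available-case comparison with losses in one arm only. A mixed model that uses the 6-month values could recover part.

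**4. Power, illustration only**

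Section 12.2 gives SD 0.17, 90% power, a 0.05 significance level and 25% attrition. Before clustering, n = 2 × (1.960 + 1.282)² × 0.17² / 0.087² = 80.3, so 81 per arm. The text shows no resulting total, cluster size or number of clusters, so there is no stated figure to reproduce.

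If a share p in both arms is lost on top of the 25%, n becomes 81 × (0.75 − p)/0.75:

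- p = 2%: 78.8, power 89.5%
- p = 5%: 75.6, power 88.2%
- p = 10%: 70.2, power 85.8%

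This ignores clustering. With the number of clusters fixed and an intra-cluster correlation of 0.24, losing members within clusters costs less power than this.

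**5. The adherence interaction**

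Write the model as Y = b0 + b1·T + b2·A + b3·T·A, with T = 1 for intervention and A for adherence to a component.

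- If A is set to 0 for all controls, A and T·A are the same column. Only b2 + b3 can be estimated, which is the contrast of better with poorer adherers inside the intervention arm.
- If A is missing for controls, they drop out, T is constant, and neither b1 nor b3 can be estimated.

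Neither version yields a difference in treatment effect. The MARS score is measured in both arms, but it concerns medication in general and is itself a secondary outcome, so it does not supply a pre-treatment factor.

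**The case against.** Two stronger readings are tempting, and the documents support neither.

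A reader might infer that participants found ineligible are removed from the analysis and that ITT is broken. Sections 8.3 and 12.3 say otherwise: their data are kept and they stay in the set. The Exit CRF only records why someone left.

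A reader might also infer that controls who take up interventions are dropped from the main comparison. Section 12.4.8 calls that a sensitivity analysis, so the primary ITT analysis is unaffected. What remains is that the item excludes people from one arm on behaviour after randomisation and sits in a list of subgroups.

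On the ineligibility rule, the best defence is that its label speaks of discovering ineligibility, which most naturally means an enrolment error found late. Eligibility is assessed only at screening in the schedule, and no repeat dementia screen is planned. This stands as a reason to expect few cases. It does not settle the wording, and even a true enrolment error leaves a randomised participant without later outcomes.

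It is also tempting to say that ineligibility would be found more often in the intervention arm because of monthly clinical contact. The medication reviews and physiotherapy sessions do belong to the package, but sections 9.2 and 10.4 describe monthly checks for participants generally. A difference between arms is conjecture, and so is a bias towards benefit.

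On adherence, the exploratory label is fair, and the list already contains one item that is not a subgroup, so interaction terms may not have been meant for every entry. That limits the consequence, but an exploratory label does not make the term estimable.

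**Conclusion.** Two points hold.

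- **Follow-up of participants found ineligible: cheap improvement.** The plan creates avoidable missing primary outcomes in people it counts as ITT. The loss may be related to outcome; direction and size cannot be determined from the documents. The range of 0.002 to 0.030 rests wholly on assumed rates and utility gaps, on losses confined to one arm, and on an available-case comparison.
- **Adherence interaction: wrong as written.** It cannot be estimated as a difference in treatment effect, and it sits badly with section 12.4.1, which treats adherence as a mediator. The consequence is confined to an exploratory analysis.

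The contaminated-control item is minor and concerns placement and labelling. Neither it nor the adherence item changes the primary ITT analysis.

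**What to change.** 1. In section 8.2 and the Exit CRF, state that participants found ineligible after enrolment remain, with consent, in the scheduled 6- and 12-month outcome assessments and in the ITT analysis, with the reason recorded. Whether they continue the intervention is a separate matter under section 8.1.
2. In section 12.4.8, remove adherence from the interaction list. Report it descriptively within the intervention arm, or as the exploratory mediator named in section 12.4.1.
3. Move the exclusion of contaminated controls out of the subgroup list and label it a supplementary non-ITT analysis open to selection bias. A complier-average model is another option, but it brings its own assumptions and is a preference, not a requirement.

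The cost is wording, plus a few extra assessments at visits already in the schedule.
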